## Source data archiving

The investigator should archive all study data for at least 15 years after the end of the study.

At the end of the study, the investigator shall also receive a copy of the data for each patient in the investigator's centre sent by the sponsor.

#

**List of abbreviations**

| **Abbreviation or Specialist Term** | **Explanation** |
| --- | --- |
| *AE* | *Adverse event* |
| *ALT* | *Alanine aminotransferase* |
| *AST* | *Aspartate aminotransferase* |
| *CI* | *Confidence interval* |
| *CRF* | *Case Report Form* |
| *DSMB* | *Data and Safety Monitoring* |
| *ECMO* | *Extra Corporeal Membrane Oxygenation* |
| *FAS* | *Full Analysis Set* |
| *ICU* | *Intensive care unit* |
| *ITT* | *Intent-to-treat* |
| *mITT* | *Modified Intent-To-Treat* |
| *N* | *Number of subjects* |
| *NEWS* | *National Early Warning Score* |
| *PP* | *Per protocol* |
| *RT-PCR* | *Reverse Transcriptase Polymerase Chain Reaction* |
| *SAE* | *Serious adverse event* |
| *SAP* | *Statistical analysis plan* |
| *SARS-Cov-2* | *Severe acute respiratory syndrome coronavirus 2* |
| *SAS* | *Statistical Analysis System (by SAS Institute)* |
| *SD* | *Standard deviation* |
| *SOC* | *Standard-of-care* |
| *WHO* | *World Health Organization* |

# Introduction

## Background and rationale

Early inhibition of entry and replication of the severe acute respiratory syndrome coronavirus 2 (SARS-CoV-2) is a very promising therapeutic approach. Polyclonal neutralizing antibodies offers many advantages such as providing immediate immunity, consequently blunt an early pro-inflammatory pathogenic endogenous antibody response and lack of drug-drug interactions1–3.

Because a suboptimal endogenous early antibody response with regard to SARS-CoV-2 replication in severe cases is observed, neutralising antibody treatment can be very interesting for patient with COVID-19 induced moderate pneumonia4,5.

A new polyclonal humanized anti-SARS-CoV2 antibodies (XAV-19) is being developed by Xenothera, which can be administered as intravenous treatment. XAV-19 is a heterologous swine glyco-humanized polyclonal antibody (GH-pAb) raised against the spike protein of SARS-CoV-2, inhibiting infection of ACE-2 positive human cells with SARS-CoV-2. Pharmacokinetic and pharmacodynamic studies have been performed in preclinical models including primates and a First In Human study with another fully representative GH-pAb from Xenothera is ongoing in volunteer patients recipients of a kidney graft. These studies indicated that 5 consecutive administrations of GH-pAbs can be safely performed in humans.

The objective of this 2-steps phase 2 randomized double-blind, placebo-controlled study is 1) to define the optimal and safety XAV-19 dose to administrate in patients with COVID-19 induced moderate pneumonia ; 2) to show the clinical benefit of selected dose of XAV-19 when administered to patients with COVID-19 induced moderate pneumonia.

In the first phase (2a) of this study, the terminal half-life (median, range) was estimated at 11.4 (5.5-13.9) days for 2 mg/kg of XAV-19 at day 1. Serum XAV-19 concentrations were above the target concentration of 10 µg/mL (tow fold the in vitro 100% inhibitory concentration [IC100]) from the end of perfusion to more than 8 days for XAV-19 2 mg/kg at day 1. No hypersensitivity or infusion-related reactions were reported during treatment and there was no discontinuation for adverse events and no serious adverse events related to study drug. In this phase 2a study, XAV-19 was well tolerated in patients admitted to hospital for COVID-related moderate pneumonia. The pharmacokinetic results of a single infusion of 2 mg/kg suggest that this dose has the potential to successfully block viral diffusion and supports the selection of this regimen for the phase 2b trial.

The statistical analysis plan described here only tackles the second step of this study.

## Study objectives

### Primary Objective

To evaluate the efficacy of XAV-19 + standard-of-care (Soc) therapy compared with placebo + Soc therapy for treatment of COVID-19 assessed by the proportion of patients who die or develop respiratory failure between baseline and Day 15.

### Secondary Objectives

**The key secondary objectives** are to evaluate the efficacy of XAV-19 + standard-of-care (Soc) therapy compared with placebo + Soc therapy for treatment of COVID-19 between baseline and Day 8, and then between baseline and Day 29.

**The others secondary objectives** are to evaluate clinical efficacy and safety of the investigational therapeutic compared to the control arm, assessed by:

**Clinical severity**:

a) National Early Warning Score (NEWS) over 29 days:

- Change from baseline to Day 3, 5, 8, 15 and 29

- Time to discharge or a NEWS <=2 and maintained for 24 hours

b) 8-point ordinal scale over 29 days

- Time to improvement of one category from baseline

- Time to respiratory failure

- Mean change in ordinal scale from baseline to Day 3, 5, 8, 15 and 29

- Percentage of subjects reporting each severity rating on an 8-point ordinal scale at Day15

c) Improvement of clinical and biological parameters over Day 15

d) Oxygenation

- Duration of oxygen therapy over 29 days

- Time to weaning in supplemental oxygen

- Proportion without O2 requirement at D8, D15 and D29

e) Non-invasive ventilation, high-flow oxygen

- Non-invasive ventilation/high flow oxygen use up to Day 29

- Incidence and duration of non-invasive ventilation or high flow oxygen use during the study

- Time to first day with non-invasive ventilation/high flow oxygen

f) Invasive mechanical ventilation / Extra Corporeal Membrane Oxygenation (ECMO)

- Ventilator / ECMO use up to Day 29

- Incidence and duration of new mechanical ventilation or ECMO use during the study

- Time to first day with Invasive Mechanical Ventilation / extracorporeal membrane oxygenation

g) Transfer to ICU by Day 29

h) Hospitalization

- Hospital length of stay (in days)

i) Mortality

- Mortality rate at day 15 and at Day 29 and at Day 60

j) Thrombotic events

- Cumulative incidence of thrombotic events: venous, pulmonary embolism, arterial thrombotic events.

**Safety of XAV-19**

Evaluate the safety of the intervention through 29 days and 60 days of follow up as compared to the control group as assessed by:

- The cumulative incidence of SAE

- The cumulative incidence of grade 3 or 4 AE

- Proportion of discontinuations or temporary suspensions of infusion (stopping without restarting, temporary suspension)

- Changes in white cell count, hemoglobin, platelets, creatinine, ALT, AST, over time

- The cumulative incidence of major or opportunistic bacterial or fungal infections

- The cumulative incidence of hypersensitivity reactions and infusion reactions

**Exploratory analysis in all patients**

- Change in SARS-CoV-2 status (positive or negative viral load) over time
- Time to RT-PCR virus negativity in nasopharyngeal swab samples over 29 days

## Endpoints

### Primary criterion

Patients who died or develop respiratory failure, as defined by the requirement of noninvasive ventilation, high-flow oxygen devices, invasive mechanical ventilation (corresponding to a score of 5 or more on the WHO 8 point ordinal scale*), or patients with low oxygen delivery device and a flow ≥ 10 L / min with reservoir.

Efficacy will be evaluated between baseline (D1 before infusion) and Day 15.

*Cf §5.1.2

### Secondary criteria

**The key secondary endpoints are the**:

Proportion of patients who die, develop respiratory failure, as defined by the requirement of noninvasive ventilation, high-flow oxygen devices , invasive mechanical ventilation, or patients with low oxygen delivery device and a flow ≥ 10 L / min with reservoir between baseline and Day 8, between baseline and Day 29.

**The other secondary endpoints are:**

1. National Early Warning Score (NEWS) assessed while hospitalized and on Day 15 and Day 29
2. Clinical status using the 8-point ordinal scale assessed daily until Day 29
3. Temperature and blood analysis between baseline and Day 15, and Day 29
4. Days of oxygen therapy over 29 days

PaO2 / FiO2 at baseline, Day 5, Day 8, Day 15, Day 29 if available

1. Days of non-invasive ventilation or high flow oxygen (if applicable) up to Day 29
2. Days of invasive mechanical ventilation/ECMO (if applicable) up to Day 29
3. Transfer in ICU
4. Hospital length of stay (in days)
5. All-cause mortality evaluated between baseline and Day 15 and between baseline and at Day 29 and at Day 60
6. Thrombotic events (peripheral venous, pulmonary, arterial)

**Safety of XAV-19 evaluated as:**

- Occurrence of all suspected XAV-19 related adverse effects or Incidence of serious adverse events

- Study drug discontinuation or temporary suspension of infusion

- Proportion of participants with treatment emergent adverse events leading to study drug discontinuation

- Incidence of major or opportunistic bacterial or fungal infections

- Incidence of hypersensitivity reactions and infusion reactions

- White cell count, hemoglobin, platelets, creatinine, ALT, AST, on D1, D3, D5, D8, D15 and D29

**Exploratory analysis:**

- SARS-CoV-2 status (positive or negative RT-PCR) over time (D1, D8, D15, and D29)

- SARS-CoV-2 status viral load over time (D1, D8, D15, and D29)

# Study Methods

## Trial design

The phase 2b will be a double-blind, placebo-controlled randomized study to assess clinical benefit and safety of the phase 2a selected dose of XAV-19 in 398 hospitalized adults with COVID-19 associated moderate pneumonia.

The study is a multicenter trial that will be conducted in up to approximately 40 sites globally. The study will compare an investigational therapeutic agent to a control arm.

Patients will be randomized to either XAV-19 or placebo in a 1:1 ratio and will receive a single dose based on the analysis of the Phase 2a study. Randomization will be stratified by site and duration since onset of COVID symptoms (1 to 6 days, 7-10 days and 11-14 days).

An independent Data and Safety Monitoring Board (DSMB) will actively monitor interim data to make recommendations about early study closure.

## Study Population

### Inclusion criteria

1. Willing and able to provide written informed consent prior to performing study procedures
2. Male or female ≥ 18 years
3. Hospitalized for COVID-19
4. Documentation of SARS-Cov-2 infection before enrolment, by positive SARS-CoV-2 RT-PCR or antigen in any body specimen (nasopharynx, oropharynx, saliva, sputum, bronchoalveolar lavage …) before enrolment
5. Evidence of pulmonary involvement (on lung examination [rales/crackles] and/or chest-imaging [Chest X-ray or computed tomography])
6. Requiring O2 supplement ≤ 6L/min at screening
7. Requiring O2 supplementation with SpO2 ≥ 92% on O2 therapy at screening (or ≥ 90 % if chronic obstructive pulmonary disease)
8. First onset of COVID-19 symptoms ≤ 14 days, among fever and/or chills, headache, myalgias, cough, shortness of breath, whichever as occurred fist (other symptoms such as asthenia not to be considered in this list)
9. WOCBP must have a negative urinary pregnancy test the day of inclusion
10. All sexually active male subjects must agree to use an adequate method of contraception throughout the study period and for 90 days after the last dose of study drug and agree to no sperm donation until the end of the study, or for 90 days after the last dose of XAV-19, whichever is longer
11. Patients with French social security

### Non-inclusion criteria

1. Evidence of multiorgan failure (severe COVID-19)
2. Mechanically ventilated (including ECMO)
3. Receipt of immunoglobulins or any blood products in the past 30 days
4. Psychiatric or cognitive illness or recreational drug/alcohol use that in the opinion of the investigator, would affect subject safety and/or compliance
5. End-stage renal disease (eGFR < 15 ml/min/1,73 m^2^)
6. Child-Pugh C stage liver cirrhosis
7. Decompensated cardiac insufficiency
8. Known allergy, hypersensitivity, or intolerance to the study drug, or to any of its components
9. Females of childbearing potential without contraceptive method, or with positive pregnancy test, breastfeeding, or planning to become pregnant during the study period
10. Current documented and uncontrolled bacterial infection.
11. Prior severe (grade 3) allergic reactions to plasma transfusion
12. Patient participating in another interventional clinical trial
13. Life expectancy estimated to be less than 6 months
14. Patient under guardianship or trusteeship
15. Patient already included
16. Prior hospitalisation in intensive care unit for the current covid-19 episode

## Intervention

The intervention is an infusion at D1.

Patients will be treated once with XAV-19 (at day 1) and monitored regularly during the study period (see flow chart). Patients will be hospitalized at least from Day 1 to Day 3, if discharged before Day 5 the patient will come back for on-site visits Day 8 and Day 15.

## Randomization

Enrollment and randomization of subjects is done online, using the eCRF, the day of the infusion or the day before.

Eligible subjects will be randomized and assigned in a 1:1 ratio to either Xav19+Soc or placebo+Soc, with stratification by site and by duration since onset of COVID symptoms (1-6 days, 7-10 days, 11-14 days).

## Randomization will be double-blinded and balanced by blocks.Stopping guidance - Critical COVID and death follow-up

During the phase 2b study, the DSMC will regularly meets as defined in the DSMC charter and may decide to stop the study prematurely.

Three meetings will be scheduled after the inclusion of D29 of the 50^th^, 150^th^ and 300^th^ patient. Rates of invasive mechanical ventilation and death will be presented and any other information asked by the DSMC.

If the proportion of patients with need of invasive mechanical ventilation and/or death after inclusion reaches to 20% or above (analyzed by incremental groups of 50 patients), the DSMC will be asked to review the data without stopping the study.

If the proportion of patients dead and/or requiring post-enrolment invasive mechanical ventilation after inclusion reaches 35% of above of the patients included in the study (analyzed by incremental groups of 50 patients), the enrolments will be temporarily discontinued and DSMC will be asked to review the data and decide on an early permanent discontinuation of the study.

References:

- study ACTT-1 (Beigel JH. NEJM 2020; 383:1813-26)

- study GS-US-5773 (Goldman JD. NEJM 2020; 383:1827-37)

- study CORIMUNO-TOCI (Hermine O. JAMA Intern Med 2020; Oct 20 (online ahead of print)

The number of patients requiring mechanical ventilation after inclusion will be tracked over time.

The thresholds requiring DSMC intervention or premature discontinuation of the study have been defined in incremental groups of 50 patients as follows

| Number of patients included | Number of patients requiring invasive mechanical ventilation after inclusion (after randomization) | |
| --- | --- | --- |
|  | For DSMC intervention | For temporary discontinuation of the study |
| Up to 50 | 10 | 18 |
| 51 to 100 | 20 | 35 |
| 101 to 150 | 30 | 53 |
| 151 to 200 | 40 | 70 |
| 201 to 250 | 50 | 88 |
| 251 to 300 | 60 | 105 |
| 301 to 352 | 70 | 124 |
| 353 to 398 | 80 | 140 |

These criteria applied to this day may need to be modified according to the evolution of the epidemic.

A definitive or temporary discontinuation of all or part of the study may be decided by ANSM, the Ethics Committee, the Sponsor after Data and Safety Monitoring Committee (DSMC) opinion.

In any case:

- A written confirmation of this early discontinuation of the study shall be sent to the coordinating investigator of the study (specifying the reasons for the early discontinuation),

- All the patients included in the study shall be informed and should attend their early withdrawal visit.

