## Sample size calculation

In the phase 2b, about 398 randomized patients, 199 patients in each group, will be included.

Assuming a true treatment difference in clinical failure rate of 10% for XAV-19 added to SoC therapy compared to placebo added to SoC therapy where a rate of 20% is expected, a sample size of 398 participants provides at least 80% power that the primary analysis will be statistically significant at the two-sided 5% significance level.

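### The 301 to 352 row of the Phase 2b stopping table is internally inconsistent: one of its two counts is off by one event, whichever denominator is meant

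*Combined protocol and SAP*

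**What the plan says.** SAP 2.5 (stopping guidance) sets two triggers for Phase 2b. A DSMC review that does not halt the study is requested when the proportion with "need of invasive mechanical ventilation and/or death after inclusion reaches to 20% or above (analyzed by incremental groups of 50 patients"). Enrolment is paused, and the DSMC decides on permanent closure, when that proportion "reaches 35% of above of the patients included in the study (analyzed by incremental groups of 50 patients"). The protocol states the same rule in 1.2.4 and 6.7.3.

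The thresholds then "have been defined in incremental groups of 50 patients as follows", in an eight-row table giving a review count and a pause count for each band of patients included. The first six bands end at multiples of 50. The seventh reads "301 to 352 | 70 | 124" and the eighth "353 to 398 | 80 | 140". Protocol 6.7.3 prints the same rows. Neither document explains the limit of 352, gives a rounding rule, or says whether the percentages or the counts prevail if they differ.

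**The concern.** The counts are the working form of the harm triggers, so each should be the smallest whole number of patients that meets the written percentage for its band. In the seventh row the two counts point to different denominators.

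What is at stake is a case where text and table instruct differently. Counting events as the text does, 70 events among 352 patients would prompt a DSMC review under the table but not under the text. If the group is instead taken to close at 350, 123 events would pause enrolment under the text but not under the table. Only one of these can arise, depending on where the band is meant to end.

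**Working it through.** **Inputs.** Trigger percentages of 20% and 35%, groups of 50, and the printed bands and counts (protocol 6.7.3; SAP 2.5). Total of 398 patients (SAP, Sample size calculation: "In the phase 2b, about 398 randomized patients, 199 patients in each group, will be included").

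**Formula.** For a group ending at n patients, the smallest count meeting the rule is 0.20 × n, rounded up, for review, and 0.35 × n, rounded up, for the pause.

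**Step 1: reproduce the table at each band's printed upper limit.**

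| n | 0.20n | rounded up | printed | 0.35n | rounded up | printed |
|---|---|---|---|---|---|---|
| 50 | 10 | 10 | 10 | 17.5 | 18 | 18 |
| 100 | 20 | 20 | 20 | 35 | 35 | 35 |
| 150 | 30 | 30 | 30 | 52.5 | 53 | 53 |
| 200 | 40 | 40 | 40 | 70 | 70 | 70 |
| 250 | 50 | 50 | 50 | 87.5 | 88 | 88 |
| 300 | 60 | 60 | 60 | 105 | 105 | 105 |
| 352 | 70.4 | **71** | **70** | 123.2 | 124 | 124 |
| 398 | 79.6 | 80 | 80 | 139.3 | 140 | 140 |

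Fifteen of the 16 cells agree. The one miss is the review count at 352: 70/352 = 19.89%, while 71/352 = 20.17%. The pause count is right there: 124/352 = 35.23% and 123/352 = 34.94%.

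**Step 2: use multiples of 50 instead (350 and 400 for the last two rows).** At 350, 0.20 × 350 = 70, as printed, and 0.35 × 350 = 122.5, giving 123 against a printed 124. At 400 the results are 80 and 140, as printed. Again 15 of 16 cells agree, but the miss is now the pause count: 123/350 = 35.14% already meets the rule, and 124/350 = 35.43%.

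**Step 3: try other rounding.** Rounding to the nearest whole number at the printed limits gives 70 and 123 at 352, and 80 and 139 at 398, so it misses two printed pause counts (124 and 140). Rounding down misses more, for example 87 where the table has 88 ("201 to 250 | 50 | 88"). No single denominator, with one rounding rule for both columns, gives 70 and 124 together.

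**Step 4: size.** Assume independent patients with a common event rate (exact binomial).

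- True rate 20%, n = 352: the chance of reaching the review count is 0.543 with 70 and 0.489 with 71.
- True rate 35%, n = 350: the chance of reaching the pause count is 0.498 with 123 and 0.453 with 124.

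These rates sit at the triggers themselves, close to where one event makes the most difference.

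**Step 5: sample size.** A failure rate of 20% against 10%, at two-sided 5% and 80% power, gives 199 per arm, or 398 (power 0.800). This row does not enter that calculation.

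**The case against.** The best defence is that the table can be read to the letter. The only printed limit is 352, and there the pause count is the correct minimum. The remaining error, a review asked for one event early, is on the cautious side and does not stop the study. Rounding the review column to the nearest number and the pause column up would even reproduce all 16 cells. That explains how the 70 may have arisen, but 70/352 is still below 20%, so the row still departs from the written rule.

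The practical weight is small, and that part of the defence stands. No test or alpha is attached to the counts, the DSMC meets on its own schedule and may ask for any data, and the criteria may be revised as the epidemic evolves. None of this explains a mismatch within the current table.

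Three stronger readings are tempting, and the documents do not support them:

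- **Both counts are wrong.** At 352 only the review count is off; at 350 only the pause count is.
- **The rule names a look at 350 patients.** It does not. That look follows from groups of 50 but is printed nowhere.
- **The last two bands (52 and 46 patients) are both errors of increment.** With 398 patients a short last group is unavoidable. Only the limit of 352 departs from the stated increment.

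A reader might also apply the counts at every running total, where gaps are far larger: 18 of 51 patients is 35.3%, yet the table asks for 35. Analysis by groups points to the end of each band, which is the reading used here.

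**Conclusion.** The row is inconsistent as written, in both documents, by one event in one cell. Which cell depends on an upper limit that the documents leave unclear. At 352 the table triggers review one event early. At 350 it triggers the pause one event late. Mixed denominators are the simplest explanation, but the finding does not depend on how the row came about.

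It rests on two assumptions: that counts are judged at the end of each band, and that they are meant to implement the written percentages. The table's column heading counts only invasive ventilation, whereas the text counts ventilation or death. That is a separate discrepancy and does not repair this row. Nothing here bears on whether 20% and 35% are suitable triggers. This is a minor correction.

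**What to change.** Reconcile the row with the written 20% and 35% rules on one denominator, in identical form in protocol 6.7.3 and SAP 2.5. Two versions are arithmetically consistent:

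- 301 to 350 with 70 and 123, followed by 351 to 398 with 80 and 140; or
- 301 to 352 with 71 and 124, leaving the last row as it is.

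The choice is the sponsor's. The first version changes one count and two band limits; the second changes one count. Either is an edit of one or two table rows in each document, with no effect on sample size, data collection or analysis.

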## Timing of final analysis

Unblinding will be performed when all data of Day 29 for all randomized patients in the main study (patients of the terminal ancillary study will not be considered) will be collected and monitored. However, the treatment allocation will only be communicated to all sites when D60 data for all patients are collected and monitored, and the data base is frozen. The analyses of the primary outcome and a series of key secondary outcomes will be produced after unblinding to allow quick scientific communication.

The final analyses of all outcomes, concerning all patients of the phase 2b study, will be performed on the final full locked database and provided in the final report.

